## Abstract

**Background:**

Excess alcohol consumption has serious adverse effects on health and violence-related harm. In the UK around 37% of men and 29% of women drink to excess and 20% and 13% report binge drinking. The potential impact on population health from a reduction in consumption is considerable. One proposed method to reduce consumption is to reduce availability through controls on alcohol outlet density. In this study we investigate the impact of a change in the density of alcohol outlets on alcohol consumption and alcohol-related harms to health in the community.

**Methods/Design:**

A natural experiment of the effect of change in outlet density between 2005–09, in Wales, UK; population 2.4 million aged 16 years and over. Data on outlets are held by the 22 local authorities in Wales under The Licensing Act 2003.

The study outcomes are change in (1) alcohol consumption using data from annual Welsh Health Surveys, (2) alcohol-related hospital admissions using the Patient Episode Database for Wales, (3) Accident & Emergency department attendances between midnight–6am, and (4) alcohol-related violent crime against the person, using Police data.

The data will be anonymously record-linked within the Secure Anonymised Information Linkage Databank at individual and 2001 Census Lower Super Output Area levels. New methods of network analysis will be used to estimate outlet density. Longitudinal statistical analysis will use (1) multilevel ordinal models of consumption and logistic models of admissions and Accident & Emergency attendance as a function of change in individual outlet exposure, adjusting for confounding variables, and (2) spatial models of the change in counts/rates of each outcome measure and outlet density. We will assess the impact on health inequalities and will correct for population migration.

**Discussion:**

This inter-disciplinary study requires expertise in epidemiology and public health, health informatics, medical statistics, geographical information science, and research into alcohol-related violence. Information governance requirements for the use of record-linked data have been approved together with formal data access agreements for the use of the Welsh Health Survey and Police data.

The dissemination strategy will include policy makers in national and local government. Public engagement will be through the Clinical Research Collaboration-Cymru "Involving People" network, which will provide input into the implementation of the research.

## Background

Excess alcohol consumption has many adverse effects on health including liver cirrhosis [1], cancer of the oral cavity, pharynx, larynx, oesophagus, liver [2] and breast [3], high blood pressure [4] and stroke [5]. There is also an increased risk of harm resulting from violence including homicide [6], suicide [7], road traffic accidents [8], domestic violence [9], and attendance at Emergency Departments and Minor Injuries Units for treatment of violence-related injuries [10].

Binge drinking is typically defined as consuming double the guideline limits in a single day during the previous week [11]. It is an increasing problem, particularly rising in young women [12], and is associated with anti-social behaviour [13] and around one-half of all violent crimes in the UK [14,15]. Binge drinking places an acute burden on the NHS as around 20–40% of all people presenting to accident and emergency departments are intoxicated, increasing to 80% after 12am [13]. Epidemiological evidence also suggests that binge drinking may reduce the benefits of moderate alcohol consumption on coronary heart disease risk [16,17].

Recent data show that around 37% of men and 29% of women exceed current UK guidelines for safe levels of alcohol consumption (defined in women as > 3 units per day; men > 4 units per day) and 20% of men and 13% of women binge drink (defined in women as > 6 units per day; men > 8 units per day) [18]. Given the wide range of harm resulting from this substantial level of excess consumption, the potential impact on health at the population level from a reduction in consumption is considerable. One of the principal evidence-based policies recently recommended by the British Medical Association to reduce alcohol consumption is to reduce easy access to alcohol through controls on hours of sale and outlet density [19,20]. In this study we focus on alcohol availability measured as outlet density in response to the National Institute for Health Research (NIHR) commissioning brief PHR no. 09/3007.

### Outlet density and alcohol-related harm

A recent systematic review of 44 cross-sectional studies found that the most frequently investigated alcohol-related harm was violent crime, especially assault [21]. The majority of studies (36/44) were from the USA. High outlet densities were associated with a higher rate of assault, self-reported injuries, car crashes, and high rates of pedestrian collisions. Higher outlet density was also shown to be associated with increased domestic violence and child abuse.

Very few studies in the review investigated associations between outlet density and non-injury health outcomes; two studies suggested high outlet densities were associated with an increased rate of sexually transmitted infections (STI) and two out of three studies found an association with high levels of consumption [21]. Of two additional American studies not included in the review, one found an association between higher outlet density and increased alcohol-related hospital admissions in San Diego County, USA [22], and the second study, set in California and Louisiana, found an association with increased self-reported liver disease, STI, and violence [23].

### Change in outlet density and alcohol-related harm

A recent review article, which included papers published up to 2006, summarised the effects of a change in outlet density resulting from three groups of studies: interrupted time series; natural experiments from alcohol bans, and changes in licensing arrangements. None were set in the UK. Many of these studies were old and few accounted for spatial autocorrelation in their analyses (i.e. the lack of independence of proximal small-areas). This review did not include any methodological assessment of the measurement of outlet density. The overall conclusion was that an increase in outlet density was associated with increased consumption and inter-personal violence, but the evidence was weaker for an association with motor vehicle crashes [24].

A further ten studies have investigated associations between change in outlet density and a limited range of outcomes, namely violence [25-31], STI’s [32,33] and suicide [34].

A six-year longitudinal study of change in outlet density set in California found that increases in bar and off-licensed outlet densities were positively related with an increase in the rate of violence, defined as a hospital admission with an overnight stay with ICD-9 ‘E-code’ E960-969 for injuries resulting from inter-personal violence, which are not alcohol-specific [25]. Using the same dataset a second paper reported that change in each measure of outlet density was positively related to likely alcohol-related accident rates, using Police-recorded crashes judged to include alcohol, and hospital admissions resulting from motor vehicle crashes identified from ICD-9 codes E810-E825 (which again are not alcohol-specific) [26]. A smaller study of alcohol-related crashes two years before and after closure of drive-up alcohol outlets in New Mexico reported a non-significant association [27].

A time series analysis of Norwegian data from 1960 to 1995 found outlet density was significantly associated with violent crime [28]. A study set in Melbourne found that an increase in the number of outlets over a nine-year period was positively related to an increase in numbers of violent assaults recorded by the Police as taking place between 8pm and 6am (used as a proxy for alcohol-related assault for which specific data were not recorded) [29]. The fixed effects analyses, which controlled for spatial autocorrelation, modelled numbers of assaults and outlets rather than rates or density. This analysis further categorised postcodes into five clusters, based on socio-demographic factors, to investigate more detailed relationships and found the strongest associations in central and inner-city suburbs.

A study set in Los Angeles reported that a reduction in alcohol availability within census tracts (resulting from a riot in 1992) was associated with a significant reduction in gonococcal infection rates [32], partially mediated by neighbourhood social capital [33]. A significant reduction was also found for violent assaults [30] but a more sophisticated statistical analysis published one year later suggested that the association reported for violent assaults was no longer significant after using a different statistical modelling method [31]. The tenth study, using the same Californian dataset, found that changes in bar and off-premise outlet densities were positively related, and restaurant densities negatively related, to attempted and completed suicide rates [34].

### Outlet density, neighbourhood deprivation and population migration

Two US papers investigated the association between outlet density and deprivation. Higher outlet densities were found in more deprived areas but paradoxically levels of consumption were highest in less deprived areas, suggesting that the mismatch between supply and demand could result in alcohol-related harm being disproportionately higher in people living in deprived neighbourhoods in proximity to alcohol outlets [35,36]. A cross-sectional study set in Glasgow, UK, found that the spatial association between outlet density and deprivation did not vary systematically, highlighting the importance of local context in the design of future studies [37]. Although it is clear from published research that selective population migration may account for a spurious widening of health inequalities over time [38,39], there are no studies which explicitly investigate this possibility for alcohol-related harm outcomes.

### Measurement of outlet density

In the longitudinal studies, outlet density was estimated simply as the number of outlets per resident population in seven of the eight studies which estimated a density [25,27-30,33,34]. One study modelled the number of outlets with the resident population as an explanatory variable [29]. Three studies estimated density using the number of road-miles [30-32]. One of these also used the geographical area as the denominator and reported no difference between the methods [30].

Although most cross-sectional papers used resident population as the denominator, one study set in California noted that there is no standard for measurement of outlet density and estimated outlet density using several different measures for the denominator, including resident population, geographical area (e.g. square mileage), and other more spatial measures of exposure to outlets including Euclidean distance from home to nearest outlet, and number of outlets per 0.5 mile ‘buffer zone’ i.e. the geographical area defined by 10–15 minutes walking time [35]. In this analysis there was little difference in the modelled associations between all of these measures. A New Zealand study used 10 minutes of travelling time by car to define a neighbourhood area, with their density measure as the number of outlets within each neighbourhood [36]. The only published UK research, from Glasgow, estimated outlet density using two different measures: outlets per 1000 residents and the mean network distance from the centroid of each small-area of interest to the nearest outlet [37].

### Primary research question

Overall, there is cross-sectional evidence from mainly American studies to suggest that higher outlet density is associated with alcohol-related harm, particularly involving violence. The evidence from longitudinal studies for associations between harm and a change in outlet density is less well established. Many methodological questions remain over the best way to measure outlet density and how to model the data. Little is known on the effect of a change in outlet density on inequalities in alcohol-related health and the role of population migration. Our primary research question for this study is:

What is the impact of a change in the density of alcohol outlets on alcohol consumption and alcohol-related harms to health in the community?

Our secondary research questions are:

1. Does a health selection effect from population migration at small-area level explain any observed associations between outlet density and alcohol-related harm?

2. What effect does change in outlet density have on population inequalities in alcohol-related health?

## Methods/Design

### Setting

The setting is Wales, UK, total population 3 million; population 2.4 million aged 16 years and over (2001 Census); with 22 local authorities (the administrative areas of local government).

### Data sources

#### Use of existing record-linked datasets: the Secure Anonymised Information Linkage databank

The Secure Anonymised Information Linkage (SAIL) databank, held and managed within the Health Information Research Unit (HIRU) at Swansea University, contains health, social and education data on three million residents of Wales and currently includes thirteen datasets containing nearly one billion records [44,45]. The smallest geographical area for which data are already linked and may be released is the 2001 Census Lower Super Output Area (LSOA) [46]. These areas vary in size but contain an average of 1500 people, with the constraint of a minimum population of 1000. There are 1896 LSOAs in Wales.

### Welsh Demographic Service (WDS)

The WDS dataset held by NHS Wales Informatics Service (NWIS), the NHS organisation in Wales mandated to hold personally identifiable data, contains addresses for all individuals who register with a General Practitioner. Dates for each update of the address record are held, thereby providing durations of residency for several different homes and the ability to link to local environment exposures at each. Demographic data may be used to create population sub-groups based on age, gender and location for the required date or duration. The WDS contains address information linked anonymously at the individual level (the anonymised linking field, ALF) which is the primary key variable for record-linkage. Using a split-file technique, NWIS supplies ALFs for the whole population of Wales to the SAIL databank [44,45].

### Residential Anonymised Linking Fields

A particular strength of the SAIL system is the development of the system for anonymising all households in Wales and linking household-level data from local authorities and others with individual health-related data whilst protecting anonymity, using Individual Anonymised Linking Fields (ALF) and Residential Anonymised Linking Fields (RALF). Address data are matched at NWIS where identifiable addresses are replaced with RALFs [47]. The residence-based metrics are then fully incorporated into the SAIL databank by linking RALFs to ALFs.

### Environment Geographic Information System

In parallel, but separate from the SAIL databank, is the Environment Geographic Information System (eGIS). The eGIS contains a number of datasets obtained from Great Britain’s mapping agency - the Ordnance Survey. These data include the Ordnance Survey Address Base Premium [48], which contains point data for all residences and businesses, both past, present and future for Wales. The Ordnance Survey MasterMap Integrated Transportation Network dataset [49] provides detailed road and footpath information and the Ordnance Survey Points of Interest database contains places that can be visited, categorised by types, such as pubs, clubs or restaurants [50]. These datasets have typically been surveyed to a spatial accuracy of ± 1-2m, providing high resolution for spatial analysis.

### Alcohol outlets

There are 22 local authorities in Wales who are responsible under The Licensing Act 2003 for maintaining public registers of Premises and Personal Licence holders, available annually from 2005. Under The Act these data are available for public inspection in council offices. Each authority keeps a database (electronic or hard-copy) of the name and address of each premise with the full unit postcode. All 22 local authorities have agreed to supply the data for this study although some authorities do not distinguish between on- and off-sales.

Using the postcode we can georeference each outlet to within any geographical boundary using standard GIS techniques. These postcodes have been validated by the local authorities and we will check each postcode to the address using the Ordnance Survey Address Base Premium [48]. In this study the basic geographical unit for small-area analyses will be the 2001 Census LSOA.

### Estimation of outlet density

Our literature review found four main approaches to estimate outlet density: (1) number of outlets per capita in an administrative unit or geographical area, (2) number of outlets per network miles per geographical area, (3) number of outlets per geographical area defined by walking or drive time (a ‘buffer zone’), and (4) closest Euclidian distance from each subject’s home to an outlet.

We wish to estimate a new measure of outlet density which includes a more realistic and robust measure of accessibility than previously published methods. We will estimate a summary statistic for distance to all outlets from each residence within a defined buffer zone. The measures of distance calculated will be network distances and travel times which will more accurately measure exposure in comparison to Euclidian distances.

We therefore propose a spatial methodology to estimate outlet density using the unique advantages of the WDS population data within the SAIL databank:

(1) We will calculate the sum (or mean) network distance for each individual to each outlet within a meaningful network range (10 minutes walk and 10 minutes drive-time) of each residence (RALF), using the service area tool in ArcGIS Network Analyst module, together with Ordnance Survey MasterMap data and point location facility data in the eGIS [49,50]. The individual-level measure of outlet density exposure will be a function (e.g. reciprocal) of the total (mean) distance;

(2) We will derive the LSOA density by averaging the values for all individual residents in the LSOA.

The primary analysis will be for all alcohol outlets but we will also estimate outlet densities for on and off-sales separately for those authorities who can supply this categorisation.

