### Statistical analysis

The primary analysis will be for all alcohol outlets but we will also analyse the data using outlet densities for on- and off-sales separately where available. Our analysis plan has to take into account the nature of the data available through SAIL. Data on individuals nested within households nested within anonymised LSOAs will be available. Our analysis plan is:

(1) Full descriptive statistics.

(2) Spatial models to explore the relationship between counts/rates of the four outcome measures and outlet density. The models will account for the year and will adjust for aggregated population characteristics, such as the percentages of males and of certain socio-economic groups, and the median age. There are a number of methodologies that could be adapted to calculate spatial autocorrelation, including the Bayesian approach of Besag, York and Mollié [56], the random effects models developed by Gruenewald and colleagues and used in the three Californian longitudinal studies [25,26,34] and geographically weighted regression (GWR) models [57-60]. Moreover, more complex methodologies which take into account network distances – the distance to an outlet based on road and footpath measurements – can be adapted to explore these relationships. These methodologies include network distance calculations [61], the two-step floating catchment technique [62-64], and modified GWR models [65]. The different types of spatial models make different assumptions, model spatial autocorrelation differently and analyse the data in different ways; their relative merits will be explored as part of the study.

(3) A multilevel analysis using the hierarchy outlined above. We will use multilevel ordinal models of the defined categories of consumption for the WHS data and multilevel logistic models of the odds of hospital admission and A&E attendance as a function of change in individual outlet exposure, adjusting for confounding individual variables (age, gender, socio-economic status) and LSOA deprivation quintile. This method cannot be used for the crime data as we only know the location of offence with no information on individuals. Multilevel modelling is a well-established technique, see for example Goldstein 2003 [66], and we will fit models using the standard MLwiN [67] and R software [68].

In order to address the secondary research questions:

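### On- and off-sales densities are restricted by authority while exposure buffers ignore authority boundaries, so typed exposure is mismeasured near non-recording authorities and the typed models cover a different area from the all-outlet model

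*Protocol article*

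**What the plan says.** Under Alcohol outlets, the article reports that all 22 local authorities will supply their registers but that "some authorities do not distinguish between on- and off-sales". How many, and which, is not stated.

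Under Estimation of outlet density, all outlets are primary, and for the split "we will also estimate outlet densities for on and off-sales separately for those authorities who can supply this categorisation". Statistical analysis repeats this: "we will also analyse the data using outlet densities for on- and off-sales separately where available".

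The same density section builds exposure from the home outwards: "We will calculate the sum (or mean) network distance for each individual to each outlet". The reach is set by travel time from the home, ten minutes on foot and ten by car. The exposure value is then defined: "The individual-level measure of outlet density exposure will be a function (e.g. reciprocal) of the total (mean) distance". LSOA density is then the average over residents. Nothing limits a buffer at an authority boundary.

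Under Environment Geographic Information System, the article describes a further source of premises type: "Ordnance Survey Points of Interest database contains places that can be visited, categorised by types, such as pubs, clubs or restaurants". It does not say that this source will be used to fill in missing licence types.

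**The concern.** Two rules operate on different geographies. Whether typed densities are estimated is decided by authority. What counts as exposure is decided by travel time from the home, whichever authority issued the licence. The rules conflict wherever a recording authority borders a non-recording one. Outlets just over the boundary are inside the resident's buffer but carry no type, so they cannot be placed in either typed density. Because the LSOA value is an average over residents, the error passes into the spatial models. Because the models concern change, an opening or closure over the boundary also leaves typed exposure unmoved if untyped outlets are dropped.

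Secondly, the typed models rest on authorities selected by how they keep registers, whereas the all-outlet model uses all 22. Under Design, the article says that authorities differ in licensing policy and that these differences are associated with density change. A difference between typed and all-outlet results could therefore come from the area covered and not from the outlet type.

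**Working it through.** The article gives no figure on this point, so there is none to reproduce. The check asks in which direction typed exposure moves when outlets across a boundary are dropped.

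**Algebra.** Let k outlets be kept, with total distance S_k and mean m_k, and let d outlets be dropped, with total S_d and mean m_d. The ratio of truncated to full exposure is:

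- Reciprocal of total distance: (S_k + S_d)/S_k = 1 + S_d/S_k, always above 1.
- Reciprocal of mean distance: m_full/m_k, above 1 if m_d > m_k and below 1 if m_d < m_k.
- Count of outlets: k/(k + d), always below 1.

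The first two are the readings that the article's own example allows. The count is shown for contrast.

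**Worked example (assumed distances).** Outlets are kept at 200, 400 and 600 m, so S_k = 1200 and m_k = 400.

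- Dropped outlets at 500, 700 and 800 m (S_d = 2000): reciprocal of total, 3200/1200 = 2.67; reciprocal of mean, 533.3/400 = 1.33; count, 3/6 = 0.50.
- Dropped outlets at 100, 150 and 250 m (S_d = 500): reciprocal of total, 1700/1200 = 1.42; reciprocal of mean, 283.3/400 = 0.71; count, 0.50.

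**Simulation.** The assumptions are not from the documents: a walking buffer of 800 m radius, straight-line distance in place of network distance, outlets uniform in the buffer, a Poisson number with mean 13, a straight boundary, and 20,000 draws per setting. Draws with no outlet left were skipped. Entries are median ratios of truncated to full exposure, except the last column.

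| Home to boundary (m) | Reciprocal of total | Reciprocal of mean | Count | Sum of reciprocals | Draws with reciprocal of mean below 1 |
|---|---|---|---|---|---|
| 0 | 2.00 | 1.00 | 0.50 | 0.50 | 49% |
| 100 | 1.78 | 1.03 | 0.58 | 0.63 | 35% |
| 200 | 1.60 | 1.05 | 0.67 | 0.74 | 22% |
| 400 | 1.30 | 1.05 | 0.81 | 0.88 | 6% |
| 600 | 1.10 | 1.02 | 0.93 | 0.96 | 0.1% |

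The reciprocal of the total was never below 1 in any draw. The error shrinks with distance from the boundary. The drive-time buffer reaches further than the walking buffer, so it would affect a wider strip; that case was not simulated.

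**Area covered.** The number of non-recording authorities is not given. Purely as an assumed range, 4 to 8 of 22 would be 4/22 = 18% to 8/22 = 36% of authorities outside the typed models.

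**The case against.** The typed analysis is additional. The article openly says that the split is incomplete and will be used only where it exists, and an article may leave the handling of buffers at boundaries to the fuller plan. This limits the importance of the point. It does not remove it, because the article does more than stay silent: it states an authority-level restriction that does not fit its own residence-based exposure.

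Several stronger readings are tempting, and the documents do not support them.

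- A reader might infer that residents near a non-recording authority get falsely low values, or values understated by half when half their outlets are over the boundary. That holds for a count or a sum of reciprocals. Under the article's example, losing outlets raises the reciprocal of total distance and can move the reciprocal of the mean either way.
- A reader might infer that the typed and all-outlet results cannot be compared at all. Outlet locations come from all 22 authorities, so the all-outlet model can be refitted on the same subset.
- A reader might infer that every LSOA within a 10-minute drive of a non-recording authority is affected. Only those with residents whose buffers contain outlets of unrecorded type are.
- A reader might take the Californian suicide study in the Background as showing opposite signs for on- and off-sales. Its contrast sets bars and off-premise outlets against restaurants, an on/off split would not separate bars from restaurants, and suicide is not an outcome here.
- A reader might assume that Points of Interest would settle the missing types. The types named are all on-sales examples, and coverage of off-sales premises or of 2005–09 is not stated.

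**Conclusion.** The point holds in a limited form. Followed as written, the plan gives mismeasured on- and off-sales exposure to residents of recording authorities whose buffers contain outlets licensed by non-recording ones. The sign of the error cannot be stated until the exposure function is fixed. For an affected resident it can be large: in the simulation, about a doubling at the boundary for the reciprocal of total distance, against almost no median change for the reciprocal of the mean. These sizes rest on the assumed geometry and on untyped outlets being dropped, which the article does not state but which follows from their having no recorded type.

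Separately, reading the typed results against the 22-authority result mixes outlet type with area, because no all-outlet fit on the matching subset is stated.

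How many residents or LSOAs are affected cannot be judged from the article. The primary all-outlet analysis is not touched.

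**What to change.** In the on- and off-sales models, exclude residences whose buffer contains any outlet of unrecorded type, at least as a sensitivity analysis. Apply this separately for the walk and drive buffers. For the survey and police outcomes, which link only at LSOA level, apply the exclusion to LSOAs using a stated rule for the share of residents affected. Refit the all-outlet model on exactly the same set, and use that fit as the comparator for the typed results. Report how many authorities lack the split and how many residences and LSOAs are excluded.

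Optionally, try to classify unlabelled premises from the eGIS data already held. Use the result only if a check in the recording authorities shows that off-sales premises and the study years are adequately covered.

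The cost is some loss of sample near boundaries in an additional analysis and one extra model run. The main fix needs no new data.
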